### Sample size

For sample size estimation for clinical trial study design, using sample size estimation as comparing parallels groups (such as three training groups: (a) T_H_:R_H_, (b) T_N_:R_H_, (c) T_N_:R_N_), and control group. A power function of 80% will be used, a level of significance of 5% and an average difference between groups of 10% will be estimated. Based on the formula described previously [40], the sample size required per group is 20. Hence, the total sample size required is 80 for the four groups, considering a drop-out rate of 10%, so the total sample size required is 88, that is, 22 individuals in each group [41].

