### Characteristics of participants

The inclusion criteria will be (1) participants aged between 30 and 69 years old and convalescent from COVID-19 (having the test with a positive diagnosis), (2) having moderate to severe symptoms, and (3) approximately 30 days since recovery from clinical signs or medical discharge (if they had been hospitalized). The exclusion criteria will be (1) exposure to high-altitude places > 1500 m in the last 3 months, (2) significant physical limitations to carry out assessments or intervention, (3) acute or chronic clinical illnesses without medical supervision, (4) anemia, (5) use of immunosuppressive drugs, (6) pregnant women, (7) hormone replacement, (8) smokers, (9) excessive use of alcohol or drugs, (10) three absents in sequence during the intervention, and (11) taking part in less than 75% of the total sessions planned.

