### Statistical analysis

After double data entry, an exploratory analysis of the data will be carried out. The primary objective will be to summarize the values, organize, and describe the data through tables with descriptive measures and graphs. Continuous variables will be expressed in terms of basic descriptive statistics (mean, median, and standard deviation), whereas categorical variables will be described in terms of frequency and percentage. The effects of the different types of training (hypoxia and normoxia), before, after 8 weeks, and after 4 weeks after the intervention, for continuous outcomes will be compared using a linear regression model with mixed effects (fixed and random). If there are binary outcomes, a cox proportional hazards model will be used to estimate the incidence rates and their respective confidence intervals, including potential confounders as covariates. The possible associations between hematological, immunological, autonomic, aerobic, and anaerobic variables will be verified with hypothesis testing and the use of other regression models. In the case of handling missing data, we will use statistical methods as multiple imputation or Bayesian methods. The level of significance will be set at 5% in all analyses.

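### The 10% drop-out allowance multiplies by 1.10 instead of dividing by 0.90, so 22 per group leaves 19.8 completers, just short of the 20 required

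*Protocol article*

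**What the plan says.** The protocol article, Sample size section, sets out the calculation in three steps.

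- Design inputs: "A power function of 80% will be used", together with "a level of significance of 5% and an average difference between groups of 10% will be estimated".
- Evaluable size: "Based on the formula described previously [40], the sample size required per group is 20". Over four groups this makes 80.
- Allowance for loss: "considering a drop-out rate of 10%, so the total sample size required is 88, that is, 22 individuals in each group".

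The Design and setting section gives equal allocation to the four groups. The Outcomes section names VO2peak as primary. The Statistical analysis section plans a linear mixed model and adds "The level of significance will be set at 5% in all analyses". The article prints no SD or coefficient of variation, does not say whether the test is one- or two-sided, and does not say which between-group comparison the 20 refers to.

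**The concern.** A drop-out allowance should leave the required number of completers once the assumed loss has occurred. Here it does not: the final enrolment figure, the requirement of 20 per group and the 10% loss cannot all hold together. The enrolment target is a number the trial relies on, and a reader would take it that 10% loss is fully covered.

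A lesser matter is that a percentage difference in a continuous outcome does not fix a sample size without a measure of spread. A reader can therefore neither confirm nor refute the 20 per group from what is printed, and cannot tell which comparison the 80% power describes.

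**Working it through.** **Inputs** (Sample size section unless noted): required completers 20 per group and 80 in total; loss d = 10%; enrolment 22 per group and 88 in total; power 80%; significance level 5%; difference 10%; allocation 1:1:1:1 (Design and setting).

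**1. Reproducing the plan's figure.** N × (1 + d): 80 × 1.10 = 88 and 20 × 1.10 = 22. Both match exactly, so this is how the figures were reached.

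**2. Applying the stated loss.** N × (1 − d): 88 × 0.90 = 79.2 and 22 × 0.90 = 19.8. Both fall just below 80 and 20.

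**3. Inflating by division.** N / (1 − d):

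- In total: 80 / 0.90 = 88.9, so 89.
- Per group: 20 / 0.90 = 22.2, so 23. With four equal groups, 23 × 4 = 92.

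The gap is one participant in total before equal groups are imposed, or one per group.

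**4. Loss that 22 per group can absorb.** 1 − 20/22 = 2/22 = 9.1%.

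**5. Cost in power.** The article gives no SD, so I assume 11.2% of the mean, a value at which the two-sided normal formula returns 20 per group: 2 × (1.96 + 0.84)² × (11.2/10)² = 19.7, rounded up to 20. Power is Φ(10 / (11.2 × √(2/n)) − 1.96).

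- n = 20: Φ(2.823 − 1.96) = 80.6%.
- n = 19.8: Φ(2.809 − 1.96) = 80.2%.

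The loss is about 0.4 points.

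**6. Secondary check: can 20 per group be reproduced?** Not directly, so I solved for the SD that would give it, reading the 10% as relative to the mean (also an assumption).

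| Reading of the calculation | SD implied by 20 per group (% of mean) |
|---|---|
| One two-sided pairwise test, 5%, t distribution (difference 0.91 SD; 10/0.909) | 11.0 |
| Same, normal approximation (difference 0.886 SD; 10/0.886) | 11.3 |
| One-sided pairwise test, 5% | 12.5 to 12.7 |
| Four-group ANOVA, depending on the pattern of means | 9.3, 11.4 or 13.2 |
| Baseline-adjusted, correlation 0.5 to 0.8 (raw SD = 11.29/√(1 − ρ²)) | 13.0 to 18.8 |

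The readings span about 9% to 19%. Under one of them only, the two-sided unadjusted pairwise test (normal approximation), power with 20 per group would be 89%, 75%, 56% and 35% at assumed SDs of 10%, 12%, 15% and 20%. None of these SDs comes from the article.

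**The case against.** The strongest reply is that the slip does not matter. Multiplying by 1 + d is a common rough convention, the shortfall is less than one participant per group, and the effect on power is negligible. The planned mixed model and the planned handling of missing data mean that an arm of 19 would not defeat the analysis. All of this stands as to size. It does not make the printed figures consistent with one another.

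A second reply is that a condensed article may leave the SD, sidedness and target comparison to the full protocol or to the cited formula. That is fair, and it is why those omissions are only a request for clarification here.

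A reader might also infer more than the article supports:

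- *That the 80% holds only for a single pairwise test with an SD of 11%.* One-sided, ANOVA and baseline-adjusted readings also give 20 per group, with other SDs.
- *That the trial is underpowered.* Nothing in the article shows that 11% is too small. Repeated VO2peak measurements, a mixed model and matching of the training groups on sex, age and conditioning could each make the relevant residual SD smaller than the raw between-person SD.
- *That power must be discounted for several contrasts.* Several are hypothesised, but the article states no adjustment such as Bonferroni, and sizing for one pairwise contrast is ordinary practice.
- *That the attendance rule ("11) taking part in less than 75% of the total sessions planned") will exhaust the 10%.* Nothing shows that the allowance leaves such losses out or that they would exceed it.
- *That 22 per group is very likely to fail.* With a 10% chance of loss for each participant, an arm of 22 keeps at least 20 with probability 62%, and all four arms do so with probability 15%. With 23 per arm the figures are still only about 81% and 42%. These describe chance variation around the expected loss, not the inflation slip.

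**Conclusion.** The drop-out step is wrong by the plan's own figures: 10% loss from 22 per group leaves 19.8, not 20. This part needs no outside assumption. The size is 88 against 89 in total, or 22 against 23 per group (92 with equal groups), and about 0.4 points of power at an assumed SD of 11.2% of the mean. It is a minor correction to a stated number and not a flaw that threatens the trial.

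Separately, the 20 per group can be neither reproduced nor refuted from what is printed. If it refers to one two-sided unadjusted pairwise t-test at 5%, it corresponds to a difference of 0.91 SD, which is 10% of the mean when the relevant SD is about 11% of the mean. That is one reading among several, and the material does not establish low power.

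**What to change.** Restate the allowance in the Sample size section without enlarging the trial, for example:

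> Enrolling 22 per group (88 in total) retains the required 20 completers per group if loss is no more than 9.1%; a loss of 10% would require 23 per group (92 in total).

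In the same paragraph, state the SD, its source, the sidedness and the comparison that were actually used to reach 20 per group. The value of about 11% should not be inserted as if it had been a design assumption, since it is only worked back from the answer. Nor should the text refer to a primary contrast unless the sponsor names one, because the article does not.

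The cost is rewording. No further enrolment is needed, and the stated tolerance for loss becomes slightly less favourable.

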### Recruitment

The invitation will be made to the Health Institutions to offer the possibility of participating in this research to patients who have had moderate to severe symptoms approximately 30 days after the recovery of clinical signs or medical discharge (hospitalized people). Furthermore, the disclosure will happen for the entire population of Ribeirão Preto, SP, Brazil, and the region through the local television channels, USP’s local radio and news from the internet, social networks, and among other media outlets. Participants will be asked to complete the evaluations on week 0. After that, they will be assigned randomly to each group. This study will develop every effort to control confounding variables. Randomization and allocation will be performed by the research coordinator. Considering special randomization techniques, in this project, we will be using the randomization of matched pairs [42], considering a baseline pairing strategy regarding confounding variables such as sex, age, and level of physical conditioning of the participants for their selection and random assignment in the research groups. As there are three training groups, (a) T_H_:R_H_, (b) T_N_:R_H_, and (c) T_N_:R_N_, pairing groups will be organized consisting of participants based on the matching characteristics above, which will be drawn randomly using Microsoft Excel for allocation to groups. This method is satisfactory and suitable for intervention studies in which there are not many participants. In terms of blinding, only the research coordinator is aware of the allocation. Different researchers will work on the intervention and collect information from the participants as evaluations, who will be blinded to avoid potential bias. To maintain the overall quality and legitimacy of the clinical trial, unblinding should occur only in exceptional circumstances when knowledge of the actual treatment is essential for further management of the patient.

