### Data collection

#### PAR-Q and anamnesis

Firstly, following what is put for people aged between 15 and 69 in the State of São Paulo Law No. 16724 of 22 May 2018, participants will answer the Physical Activity Readiness Questionnaire (PAR-Q) and those who respond positively to any of the questions, they will sign the Term of Responsibility.

Sociodemographic data, general, and specific (COVID-19) health status related to lifestyle, information on comorbidity, and drug treatment will be assessed through the Anamnesis. Answers about the symptoms associated with COVID-19 will allow assessing the intensity of the disease’s manifestation.

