## Discussion

It is plausible that the convalescent people of COVID-19 who showed moderate to severe symptoms are in the process of gradual recovery and still have changes in their health status, even after approximately 30 days of recovery from clinical signs or medical discharge. Therefore, the monitoring control group that will not train will describe the effects of COVID-19 on lung function, hematological, immunological, autonomic parameters, physical fitness, and mental health.

The gradual recovery process of the participants will be observed according to the association of training (T) and recovery (R) with hypoxia (H) or normoxia (N). Therefore, it is expected that the normoxia training and recovery group (T_N_:R_N_) can show better results compared to the control group. Besides, both groups that will train in hypoxia may demonstrate even better results than the T_N_:R_N_ group, with a higher result for the group that will perform the training in normoxia and the recovery in hypoxia (T_N_:R_H_), comparing the group that will perform training and recovery in hypoxia (T_H_:R_H_). The justification for these two groups to train differently associated with hypoxia is that exercise intensity can be reduced with hypoxia exposure. In this way, to minimize this possibility, the group that will breathe hypoxia air only during the pause could perform the training stimulus in greater intensity (normoxia).

The expectation is that physical activity can be used to face the COVID-19 pandemic and other health problems as a complementary treatment. The consolidated evidence on the benefits of physical activity for physical, physiological, social, and mental health and the knowledge generated by this research project may contribute to solving priority health problems in Brazil. Furthermore, this project’s results may contribute to the qualification of health care practices and promote scientific, technological, and innovation development in the Health area, aiming at strengthening the Unified Health System of Brazil.

Still, it is expected that the genetic variants studied may be associated with the recovery process of the convalescents of COVID-19 and with the effect of moderate training combined with intermittent normobaric hypoxia. The study of genetic variants can bring important advances in understanding the variation in responses related to the triggering and progression of some diseases and the effect of physical training.

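### Acute COVID-19 severity is collected but not named in the matching or in the VO2peak model: this costs precision between the training arms and may bias the comparison with the self-selected control group

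*Protocol article*

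**What the plan says.** The Discussion presents it as plausible that people with moderate to severe illness "are in the process of gradual recovery and still have changes in their health status" about a month after recovery or discharge. The inclusion criteria (Characteristics of participants) ask for "having moderate to severe symptoms" and "approximately 30 days since recovery from clinical signs or medical discharge (if they had been hospitalized"). The starting event therefore depends on whether the person was hospitalised, and no window is set around the 30 days.

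Under Recruitment, randomisation uses matching, "considering a baseline pairing strategy regarding confounding variables such as sex, age, and level of physical conditioning of the participants". The text then says that "pairing groups will be organized consisting of participants based on the matching characteristics above" and describes this for the three training arms. Design and setting forms the control group differently, from people who cannot take part in the training but agree to be assessed.

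Under PAR-Q and anamnesis: "Answers about the symptoms associated with COVID-19 will allow assessing the intensity of the disease". No use of this information in allocation or analysis is stated. Statistical analysis gives continuous outcomes a linear mixed model and names no covariate. Potential confounders appear as covariates only in the sentence on the Cox model for binary outcomes.

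**The concern.** If recovery is still under way, VO2peak may change between week 0 and week 13 without any training. It is a reasonable inference, though not a statement in the protocol, that the amount of change depends on how ill the person was. Baseline conditioning is only a partial stand-in. A previously fit person weakened by severe disease and a habitually unfit person after moderate disease can have the same VO2peak at entry and different expected recovery.

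Two comparisons are affected in different ways. Between the training arms, unexplained differences in recovery stay in the residual variance, and the arms can differ in severity by chance. Against the control group, neither randomisation nor the described matching balances severity. Willingness or ability to train may itself be related to how ill someone was. The protocol relies on that comparison for its hypothesis that training in normoxia improves on no training.

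**Working it through.** **1. The plan's own figure.** Sample size gives 80% power, 5% significance, a 10% difference and 20 per group, but no SD. From n = 2(1.960 + 0.842)² SD²/10², n = 20 implies SD = 10 × √(20/2)/2.802 = 11.3 points, if the test is two-sided and the 10% is a percentage of mean VO2peak. Drop-out: 80 × 1.10 = 88, or 22 per group, as stated. The 11.3 serves below only as a scale.

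**2. Chance imbalance between training arms.** Assumption: 30-50% of participants are severe (or were hospitalised), and severity is independent of the matching variables. With X and Y independent Binomial(22, p):

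| p | P(\|X − Y\| ≥ 5) |
|---|---|
| 0.3 | 0.137 |
| 0.4 | 0.165 |
| 0.5 | 0.174 |

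A gap of 5 out of 22 is 22.7 percentage points. By simulation, at least one of the three pairs of training arms shows such a gap with probability 0.30 to 0.36. If matching on conditioning also partly balances severity, these probabilities are too high.

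**3. What such a gap does.** Assumption: severe and moderate cases differ by 5 to 10 points in spontaneous VO2peak change. The shift is 0.227 × 5 = 1.1 to 0.227 × 10 = 2.3 points. The standard error of a two-arm contrast at 22 per arm is 11.3 × √(2/22) = 3.4 points. The shift is therefore about 0.3 to 0.7 standard errors (1.1/3.4 to 2.3/3.4). It is part of the sampling variation that the standard error already describes.

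**4. What adjustment gains between training arms.** If the added covariates explain a fraction R² of the remaining variance, the SD falls to 11.3 × √(1 − R²). At 20 per arm, power goes from 80% (R² = 0) to 84%, 88% and 92% for R² = 0.1, 0.2 and 0.3. These R² values are assumptions.

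**5. The control comparison.** Here a difference in severity share would be systematic. Bias = difference in share × difference in spontaneous change. Type I error = 1 − Φ(1.96 − bias/SE) + Φ(−1.96 − bias/SE), with SE = 11.3 × √(2/20) = 3.57.

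| Difference in share | Difference in spontaneous change (points) | Bias (points) | Two-sided type I error |
|---|---|---|---|
| 0.10 | 5 | 0.5 | 5.2% |
| 0.10 | 10 | 1.0 | 5.9% |
| 0.20 | 5 | 1.0 | 5.9% |
| 0.20 | 10 | 2.0 | 8.7% |
| 0.30 | 5 | 1.5 | 7.0% |
| 0.30 | 10 | 3.0 | 13.4% |

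The target difference is 10 points. Every share and recovery difference in this table is an assumption.

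**6. Why the interaction with visit matters.** If baseline is one of the repeated measurements in the model, a severity main effect moves all visits equally and leaves the contrast in change nearly untouched. Only severity by visit lets severe and moderate cases recover at different rates.

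**The case against.** The strongest reply is that the article condenses a fuller document, and that covariate lists and visit interactions are ordinary content of a statistical analysis plan, which is not shown. The matching list is also introduced as examples. That stands as far as it goes: the documents do not show that severity was ignored, only that it is not named. Two things keep the point alive. The next sentence builds the matched groups on the characteristics just listed. And the analysis section does mention adjustment, but ties it to binary outcomes and leaves the model for the primary outcome without it.

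A second reply is that chance imbalance between randomised arms is already covered by the standard error and the 5% level. This is right. A reader might infer that the hypoxia contrasts are biased; they are not, and the case there is one of efficiency.

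A third is that the protocol provides for the natural course through concurrent arms and an untrained control group. The concurrent arms do this for the contrasts between training arms. The control group does it only as far as its members resemble those who train, and the way it is formed gives no assurance of that.

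A reader might also take the Discussion to assert that all outcomes will move without training, or take the two starting events as an eligibility error. The text says only that continuing recovery is plausible. The two starting events make participants more heterogeneous, but counting from test or symptom onset would bring its own, since long and short illnesses would then stand at different stages on the same day.

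**Conclusion.** The point holds in a limited form. Severity is collected, and the protocol gives reason to think that recovery is still under way, yet severity has no named role in matching or in the model for VO2peak.

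Between the training arms the consequence is modest. A gap of 5 or more severe cases in a given pair has probability 14-17%, and the gain from adjustment would be a few points of power (80% to 84-92%) if severity and timing explain 10-30% of the remaining variance. Against the control group the consequence could be systematic: 0.5 to 3.0 points of bias on a 10-point target, with type I error of 5.2% to 13.4%.

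These figures rest on an assumed severe share, assumed differences in spontaneous recovery, and an SD inferred from the stated sample size. They show what is plausible; they do not estimate what happened.

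**What to change.** In the mixed models for VO2peak and the other continuous outcomes, pre-specify hospitalised yes/no (or a severity grade derived from the anamnesis) as a baseline covariate, with its interaction with visit. If dates of the positive test or symptom onset were recorded, which the protocol does not say, add days from one of these events, the same for everyone, to baseline, also with visit. Tabulate both variables by arm, including control. State that in the control comparison adjustment deals only with measured differences.

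The cost is small. One binary covariate with its visit interaction takes 3 parameters over the three time points named in the analysis section (1 + 2), or 4 over the four VO2peak assessments (1 + 3). Two covariates take 6 to 8. Hospitalisation status is already needed to apply the 30-day criterion, and symptom intensity comes from the anamnesis, although a grading rule would have to be written down before the data are analysed.

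No change to the matching is worthwhile, because Trial status reports 84 participants included against a planned 88. The eligibility clock can stay as it is.

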### Design and setting

The study design is based on a randomized, double-blind controlled clinical trial composed of four groups. The control group being formed by the participants who are not available to participate in the intervention and accept to carry out a follow-up through the evaluations; and the physical training groups randomly divided according to the association of training (T) and recovery (R) with hypoxia (H) or normoxia (N): (a) T_H_:R_H_, (b) T_N_:R_H_, and (c) T_N_:R_N_. The allocation ratio will be 1:1:1:1.

As Fig. 1 shows, the experimental protocol will consist of (i) familiarization and carrying out the initial assessments (evaluation 1) in the three sessions of week 0; (ii) 8-week intervention with a partial assessment to adjust the training load on week 5 (half of the intervention – evaluation, (2) (iii) reassessments on week 9, following the end of physical training intervention (evaluation 3), and (iv) reassessments on week 13, four after the end of the intervention (evaluation 4).

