Out of the three training groups, two will be exposed to hypoxia according to the association of training (T) and recovery (R) with hypoxia (H): (a) T_H_:R_H_ and (b) T_N_:R_H_. These groups will be subjected at an inspired fraction of O_2_ (FiO_2_) to simulate approximately 3000 m of altitude in the Multisport Gymnasium. The other training group will train in normoxia (T_N_:R_N_) at FiO_2_ corresponding to sea level in the Multisport Gymnasium. Hypoxia generators will be used together with the normobaric hypoxia tents. It is important to note that O_2_ saturation will be monitored during all training sessions, which will allow us to verify the response to hypoxia during training and the application of the Lake Louise Scale.

All sessions will be developed with a group of researchers and monitored by acute responses to the training using HR, blood oxygen saturation (SPO_2_), and RPE. Weekly, acute responses will be associated with exposure to hypoxia using a questionnaire. These data will be analyzed as soon as they are collected to provide the highest safety to the participants. Any unexpected responses will be communicated to the study’s coordinator, who will be available at all the time used for intervention and evaluations. In addition, on weeks 2, 4, and 6, the blood [La-] will be evaluated to control the training load.

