### Participant timeline

This study is ongoing and started in September 2020, ending in December 2021. The schedule for enrolment, interventions, and assessments is presented in Table 2.

**Table 2 Tab2:** Schedule of enrolment, interventions, and assessments

Timepoint	Study period					
	Enrolment	Allocation	Post-allocation			
	***-t***_***1***_	0	***Baseline***	***Partial evaluation*** ***(week 5)***	***Post-training*** ***(week 9)***	***After 4 weeks of training end (week 13)***

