### Ethics

This study was approved by the School of Physical Education and Sport of Ribeirão Preto – University of São Paulo (USP) and Faculty of Pharmaceutical Sciences of Ribeirão Preto *–* USP Research Ethics Committees (CAAE: 33783620.6.0000.5659, and CAAE: 33783620.6.3001.5403, respectively). Activities will start after signing the free and informed consent term presented by the coordinator of the study. Following the Research Ethics Committee orientations, a biorepository at the School of Physical Education and Sport of Ribeirão Preto *–* USP was created to store biological samples for use in future studies depending on the participants consent (CAAE: 33783620.6.0000.5659).

All care for the safety of the participants and the work team will be taken. First, an evaluation of the health status will be carried out. The participants who do not have limitations or discomfort that may prevent the evaluations’ performance or the intervention will participate in the proposed intervention. Data will be added to a confidential dataset, and an alphanumeric code will be assigned to each participant. All local databases will be secured with password-protected access systems.

Any modifications to the protocol which may impact on the study conduction, the potential benefit of the participant or safety, including changes of study objectives, design, procedures, participant population, sample sizes, or significant administrative aspects will require a formal amendment to the protocol and will be communicated to the Brazilian Clinical Trials Registry (RBR-5d7hkv) and the Research Ethics Committees.

Authors will create scientific reports to be submitted to peer-reviewed journals. Also, information about the different outcomes will be shared in different scientific events.

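### The double-blind label cannot cover the open control group, blinding of session staff is at risk, and Table 2 contradicts the text on whether baseline precedes allocation

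*Protocol article*

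**What the plan says.** Design and setting: "The study design is based on a randomized, double-blind controlled clinical trial composed of four groups". The Abstract uses the same label. The next sentence of Design and setting forms the control group from people who are not available for the intervention and agree to attend the evaluations only. The other three groups train and are divided at random.

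Recruitment: "In terms of blinding, only the research coordinator is aware of the allocation". The sentence after it reads: "Different researchers will work on the intervention and collect information from the participants as evaluations, who will be blinded to avoid potential bias". The same section places the week-0 evaluations first and random assignment second. It forms matched sets on sex, age and level of physical conditioning before the draw.

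Instrumentation normobaric hypoxia: all three training groups use the same mask and tent arrangement, so that trained participants do not know the oxygen concentration.

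Blood oxygen saturation (SPO2): readings are recorded at rest, at the end of each effort, at the lowest point in the break and at the end of the pause. Under Intervention protocol, researchers run every session and the monitoring data are examined immediately for safety. The Discussion explains that T_N:R_H breathes hypoxic air in the pause only.

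Participant timeline, Table 2: Allocation stands at time 0, and Baseline, including VO2peak, is the first of four columns headed "Post-allocation".

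**The concern.** The primary outcome, VO2peak, comes from an incremental test that ends at voluntary exhaustion. SF-12 and DASS-21 are completed by the participant. Results of this kind can move with a participant's expectation or an evaluator's encouragement, so it matters who knows the group at testing.

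A double-blind label tells readers that this route is closed throughout the trial. If it is open for contrasts with control, those contrasts should be read as open-label. They include the first hypothesis in the Background, that normoxic training improves health status compared with no training. If session staff can infer the air mixture and also run outcome tests, the contrasts among training groups are exposed too, on the evaluator's side.

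The order of baseline and allocation matters for the same reason: a baseline effort test taken after allocation would not be protected from knowledge of the group.

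**Working it through.** No figure in the plan bears on this point, so the check sets statements side by side.

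**1. Participants.** Four groups give 4 × 3 / 2 = 6 pairwise contrasts.
- Three involve the control group. Controls do not train and know it; trained participants know that they train. None of these three contrasts is participant-blind.
- Three are among T_H:R_H, T_N:R_H and T_N:R_N. Here the common mask and tent arrangement supports participant masking, and nothing in the article contradicts it.

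**2. Session staff.** The Recruitment section says that only the coordinator knows the allocation and that the researchers on the intervention are blinded. Two features of the sessions put this at risk.
- Saturation is read at rest, effort and pause. Two groups breathe air simulating about 3000 m and one breathes sea-level air, so the readings carry information about the group.
- T_N:R_H changes air between effort and pause. Table 1 gives six sets from week 4. The stated session length confirms five pauses: 5 + 6 × 5 + 5 × 2.5 + 3 = 50.5 min. Two changes per pause make 2 × 5 = 10 changes per session for this group. The article does not say how the switching is done or concealed.

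**3. Evaluators.** The sentence on blinded researchers names the intervention and the evaluations together. It can be read as two separate teams, or as one team distinct from the coordinator. Under the second reading, a person who has seen saturation patterns in sessions could later run that participant's VO2peak test. Such a person would also recognise which participants never came to training.

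**4. Order of baseline and allocation.**

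| Source | Order |
|---|---|
| Recruitment | week-0 evaluations, then matched sets, then draw |
| Table 2 | Allocation at time 0, then Baseline |

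The two cannot both be right. Matching on conditioning needs a fitness measure before the draw, which fits the Recruitment order and suggests that the table is the slip.

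**The case against.** **Masking was planned.** Trained participants share one mask and tent arrangement, the Lake Louise questionnaire goes to normoxia and hypoxia groups alike, and the evaluators are stated to be blinded. No exercise trial can blind an untrained control group, so a reader may take the label to refer to the training groups only. This stands for participants in those groups. It does not rescue the label, which is attached to all four.

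**Operational detail.** How air is switched, and who staffs what, may be in the full protocol. This is fair. Point 2 is therefore a risk to session staff's blinding, not proof that it fails.

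**Table 2 is a layout matter.** It marks the interventions only under Baseline, so its columns are not a literal sequence. This is probably right. The table still contradicts the text and should agree with it, but it does not show that any baseline test was done unblinded.

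**Stronger readings that the documents do not support.**
- A reader might infer that the one unblinded person attends the outcome tests. The Intervention protocol section says of the study's coordinator only "who will be available at all the time used for intervention and evaluations", as the person to whom unexpected responses are reported. The evaluations are assigned to other researchers.
- A reader might infer that group is known at enrolment, because consent is "signing the free and informed consent term presented by the coordinator of the study" and "Randomization and allocation will be performed by the research coordinator". Consent comes before all activities and the draw follows the week-0 evaluations, so no draw exists at consent. Control status depends on availability, not on the draw. That the differently worded coordinator titles mean one person is likely but not stated. What remains, one person forming the matched sets and running the draw, is a question of allocation concealment, not of blinding.

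**Conclusion.** The point holds in three parts. First, the double-blind label is wrong for the four-group trial: on the participant side it fails for the three contrasts with control, on outcomes that depend on effort or self-report. This rests on the article's own description of the control group and needs no assumption. Second, among the training groups participant masking stands. The statement that only the coordinator knows the allocation is at risk for session staff, and this reaches the outcomes only if the same people also evaluate, which the article leaves open. Third, Table 2 and the Recruitment section contradict each other on the order of baseline and allocation.

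The size of any bias cannot be derived. The Sample size section gives no standard deviation and nothing in the article indicates how large an effort or encouragement effect might be. A false-positive rate would rest wholly on assumed values, so none is offered. The corrections should be made; they concern reporting and staffing and do not by themselves invalidate the trial.

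**What to change.** (a) In the Abstract and in Design and setting, replace the double-blind label with: outcome assessors blinded; training participants not told the air mixture; control group open. State that contrasts with control are interpreted as open-label. The words on outcome assessors are justified only for evaluations where (b) is met.

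(b) For all pending evaluations, have the VO2peak and other outcome tests run by team members who did not staff that participant's training sessions, and withhold the saturation and Lake Louise records from them. Safety monitoring by session staff is unchanged.

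(c) Move the Baseline column of Table 2 before Allocation, to agree with the Recruitment section.

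Cost: a less favourable label and some rescheduling within the existing team. Trial status reports 84 included against the target of 88 in Sample size, so (b) helps only evaluations still to come, while (a) and (c) apply to the whole report. Handing the draw to another person is not recommended here: on the stated target it would affect 88 − 84 = 4 participants.
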